### Statistical analysis

Statistical analysis will be performed using SPSS software 20.0, and will include descriptive data and means, confidence intervals, and the standard deviation from the mean. This will be determined for all outcome measures recorded at baseline, 12-week, and the follow-up measurement (3 months after the intervention).

The feasibility and acceptably of using pedometers as an intervention to promote ambulatory activity and improve health outcomes in this population will be evaluated through participant satisfaction with the intervention by using survey questionnaire about pedometer usage after completion the intervention. Participants will be asked about participation in the intervention, and about their satisfaction with participation. Details of the questionnaire were described elsewhere [95]. In addition, adherence to the pedometer-driven walking program by using pedometer logs to determine the number of days that pedometer was worn and divided by the total number of intervention days, and a positive change in the outcomes variable over 12-week periods.

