### Intervention protocol

The 12 week pedometer-driven walking intervention will be based on self-regulation theory (SRT) [101] and include goal setting, feedback, educational material, and the use of a step calendar for self-monitoring. Participants will be required to walk for at least five days per week to meet evidence based international guidelines that recommend adults to accumulate at least 30 minutes of moderate intensity activity, on at least five days/week, to achieve optimal health benefits [102].

#### **
*Educational materials*
**

Participants in both the walking (intervention group) and control groups will also receive standardised educational material that consists of written and graphical information describing the importance of walking as a PA for health benefits and prevention of disease [29,30].

#### **
*Goal setting*
**

At the beginning of each week, participants will receive a weekly email reminder about his or her step-count goal for that week based on their baseline walking activity level; the goal will aim to gradually increase the level of activities by 5% from their previous goal setting target with an aim to reach at least 10,000 steps per day at the end of the 12 week period. These targets are based on international guidelines for walking interventions [52]. However for those who reached 10,000 steps per day at any time during the program will be also encouraged to maintain and increase their physically active lifestyle.

#### **
*Step count and feedback*
**

Participants in the intervention group will receive permanent step-count feedback by looking at the digital display on the pedometer monitor. Participants will also receive personalized weekly emails about daily average step-count and additional health information, to encourage their adherence with the program.

#### **
*Step calendar*
**

Participants in the walking group will be given a diary to record their walks and note each day as to whether they are adhering to the program, the time of day, duration of the walk, the week’s step-count goal, and the number of steps taken at the end of each day.

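### The adherence ratio measures pedometer wear, not the walking frequency or step goals that define the programme, so it can overstate feasibility

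*Protocol article*

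**What the plan says.** In the protocol article, the Statistical analysis section lists how feasibility and acceptability will be judged. Besides a satisfaction survey, it names "adherence to the pedometer-driven walking program by using pedometer logs", and says the logs serve "to determine the number of days that pedometer was worn and divided by the total number of intervention days". The sentence then ends "and a positive change in the outcomes variable over 12-week periods", without saying whether this is part of adherence or a separate criterion.

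The Intervention protocol section describes what adherence would be to. On frequency: "Participants will be required to walk for at least five days per week". On intensity, under Goal setting, the weekly email carries a goal meant to "gradually increase the level of activities by 5% from their previous goal setting target". The same section names 10,000 daily steps or more as the level to be reached by the close of the programme. Under Step calendar, walking-arm participants keep a diary in which they "note each day as to whether they are adhering to the program". The diary also holds the time and length of the walk, the goal for the week and the day's step total.

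**The concern.** The ratio is named as adherence to the walking programme, but its numerator is days of device wear and its denominator is every day of the intervention. The two things asked of participants, walking on enough days and reaching the week's goal, can both be absent while the score stays at its maximum.

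This matters because the trial is presented as a feasibility study whose results will shape a fully powered trial. The section lists few feasibility measures: the survey, this ratio and the loosely worded outcome change. The ratio is the one that speaks most directly to whether these workers can follow the programme. If high wear is reported as high programme adherence, the larger trial may be planned on the belief that the walking was done.

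**Working it through.** The plan states no adherence figure or threshold, so there is nothing to reproduce. The check applies the stated ratio to simple patterns of behaviour.

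**Inputs**
- Length of intervention: 12 weeks (Intervention protocol).
- Required walking: at least five days a week (Intervention protocol).
- Weekly goal: 5% above the previous goal (Goal setting).
- Score: days worn / total intervention days (Statistical analysis).

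**Denominator and requirement**
- Intervention days: 12 × 7 = 84.
- Minimum walking days: 12 × 5 = 60.

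**Score under the stated ratio**

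| Behaviour | Days worn | Score |
|---|---|---|
| Worn daily, no programme walking, no goal met | 84 | 84/84 = 100% |
| Walks five days a week, meets goals, worn daily | 84 | 84/84 = 100% |
| Same walker, worn six days a week | 72 | 72/84 = 85.7% |
| Same walker, worn only on the five walking days | 60 | 60/84 = 71.4% |

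The first two rows carry the point: opposite behaviour, same score. The last two rows apply only if the walker leaves the device off on some days. Against the last row, a non-walker scores higher from 61 days of wear (61/84 = 72.6%).

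**Step goals**

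Raising the goal by 5% a week multiplies the starting value by 1.05^11 = 1.71 or 1.05^12 = 1.80, depending on whether 11 or 12 increases are counted. A participant whose steps never move from baseline can still score 100%.

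**Scoring against the five-day requirement, for illustration**

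Take walking days / 60, capped at 100%. The five-day walker scores 60/60 = 100% and the daily wearer who does no programme walking scores 0/60 = 0%. The diary fields listed in the article are enough to make this separation.

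**The case against.** - **Wear is part of the intervention.** The programme rests on self-regulation theory, with self-monitoring and feedback, and the section asks whether pedometers are feasible as an intervention tool. Wear is therefore a legitimate process measure, and since steps are logged daily, all calendar days is a defensible denominator for it. This stands, and is a reason to keep the ratio under an accurate name. It does not make wear a measure of walking.
- **The sentence also mentions positive outcome change.** A daily wearer who never walked more would show no gain in steps, and step count is a primary outcome. That is fair, but the clause does not say which outcome, how large a change, or whether it belongs to adherence. If it does, adherence is mixed with effect and can no longer help to explain a null result.
- **A journal article condenses.** Summaries of diary items may be in a fuller document, and nothing prevents their being reported. That would answer a complaint about missing detail. Here, however, the article states the numerator and denominator itself.
- **A stronger reading.** A reader might infer that the ratio ranks a non-walker above a full complier, or understates a full complier by 29 points (100% − 71%). The documents do not support this. The diary asks for each day's step total and the weekly emails report a daily average, which together imply daily wear, so a participant who follows everything ties at 100%. The reversal needs a walker who omits wear on non-walking days. That is possible, since the explicit instruction to wear the device throughout waking hours is given for screening and not restated for the 12 weeks, but it is not full compliance.

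**Conclusion.** The point holds in this form: the stated adherence ratio measures device wear and ignores both elements that define the programme. At the extreme, complete non-performance of the walking scores 100%, equal to full compliance. The 71% figure is conditional on wear being confined to walking days.

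Two assumptions lie behind the arithmetic: that intervention days means all 84 days of the 12 weeks, and that a day of wear counts regardless of steps. The article gives no minimum step count or wear time for a valid day.

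The consequence is limited. Adherence is descriptive, has no threshold or progression rule in the article, and enters no between-group comparison. A reader might infer that the trial could say nothing about whether the programme can be followed. That goes too far, because diary and step data are collected and could show it. What is at risk is the feasibility conclusion, which the ratio as labelled can make look better than the walking justifies.

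**What to change.** Reconcile the Statistical analysis and Intervention protocol sections as follows.

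1. Keep days worn / 84, but call it device-wear compliance.
2. For the walking arm, report two programme measures from the diary, kept apart because the protocol states the requirements separately:
   - (a) the proportion of the 12 weeks with a recorded walk on at least five days;
   - (b) the proportion of weeks in which mean daily steps met that week's goal.
3. Calculate each proportion per participant, then summarise across participants with a 95% confidence interval, since weeks within a person are not independent.
4. State in advance how missing diary days are handled.
5. Keep outcome change out of the adherence measure. If it is meant as a feasibility criterion, list it separately and define it. Measure (b) is itself close to the step-count outcome, so (a) is the cleaner measure of whether the programme was followed.

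The cost is a change of wording and some extra analysis of items the diary already collects. The downside is that the reported adherence will probably be lower.

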### Screening

Potential participants will initially be screened for eligibility for entry into the randomized control trial by wearing the pedometer (Yamax Digi-walker SW-200) for seven consecutive days. Participants will be instructed on how to wear and use the pedometer at the assigned location on a waist band above the lateral hip during all waking hours, except for periods immersed in water (bathing, swimming), during certain sporting activities (playing basketball or soccer, etc.), or in bed at night. They will be instructed to reset the pedometer to zero at the beginning of each day, and remove it at the end of each day, record on a step calendar the date and the time pedometer was attached and also removed, and the total number of steps displayed on the pedometer at the end of each day.

Participants who have accumulated an average of 7,500 or more steps per day will be excluded before baseline assessment. In addition, the ability of the participant to be physically able to participate in walking program will be screened using the physical activity readiness questionnaire (PAR-Q) [69]: if a participant answers yes to one or more questions on the PAR-Q, they will be advised to consult their healthcare provider and that physician consent will be required prior to program participation.

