### Sample size

Sample size calculations for effectiveness will be not performed. As this will be a feasibility study, one of the aims of data collection will be to determine the effect of the intervention which will then allow size calculations for an adequately powered RCT. However, we will invite the pool of ≈ 900 workers from a local meat processing plant on the South Island of New Zealand to consider participating in the study. Volunteer participants will be screened and the study will begin when the first 60 participants who meet eligibility criteria have been recruited (N =30 participants each group).

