## Procedure

### Preparation of participants

All potential participants will be instructed to wear the pedometer on the waistband of their clothing for seven days, based on previous study protocols [96-99] in order to establish baseline step-counts during normal daily activity. Tudor-Locke and Bassett [52] have classified pedometer-determined PA in adults by an average step count of less than 5,000 steps/day as a sedentary lifestyle, and 5,000 to 7,499 steps per day as low activity; therefore, participants who accumulate an average baseline step count of 7,500 steps per day or more will be excluded; remaining participants will be randomized to one of the two groups. Baseline outcomes measures were collected during the seven days pedometer assessment including the primary and secondary outcomes. After randomization, all participants will attend a 30 minute education session on the health benefits of being physically active, then participants in the walking group will receive a brief intervention group session of up to 70 minutes, including a 10 minute self-efficacy walk, a 30 minute session focussing on physical activity behaviour change, and 30 minutes focused on the education resource material (physical activity and PA booklet). This intervention session will be based on the Back2Activity protocols [100] and conducted by physiotherapists (including one with training in motivational interviewing), and student researcher.

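### One strand of the feasibility evaluation is a before-after change without the control arm, and for step count that change leans upward because the selection week is also the baseline week

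*Protocol article*

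**What the plan says.** The feasibility paragraph of Statistical analysis names three things. Feasibility and acceptability "will be evaluated through participant satisfaction with the intervention by using survey questionnaire about pedometer usage after completion the intervention". Adherence is then defined as days the pedometer was worn divided by intervention days. The sentence ends "and a positive change in the outcomes variable over 12-week periods". It names no outcome and no size, and it does not mention the control group.

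Under Preparation of participants, all candidates wear the pedometer for seven days "in order to establish baseline step-counts during normal daily activity", and "participants who accumulate an average baseline step count of 7,500 steps per day or more will be excluded". The same section adds: "Baseline outcomes measures were collected during the seven days pedometer assessment including the primary and secondary outcomes". The Screening section gives the same cut-off but places it differently in time: "Participants who have accumulated an average of 7,500 or more steps per day will be excluded before baseline assessment". Neither section describes a second step-count week before randomisation.

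The Control group section has control participants wear the pedometer again for a week at 12 and at 24 weeks. The Introduction states the aim and hypothesis as comparisons with the control group.

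**The concern.** A before-after change mixes any programme effect with whatever would have happened anyway. For step count, part of what would have happened anyway is predictable in direction. People are kept only if a single noisy week fell below 7,500, and that week then becomes the starting point for change. Some of those kept had an unusually quiet week and will drift back up. Truncation removes people whose week happened to be unusually busy, so nothing balances this in the mean.

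Two uses of the result are at stake. The Discussion says the findings will inform a fully powered trial, and a strand that leans positive under no effect informs that choice poorly. The Sample size section says the data will show the effect from which the later trial is sized. If the within-arm step change were taken as that effect, it would be too large and the later trial too small.

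**Working it through.** **Inputs from the article.** Cut-off 7,500 steps/day on a seven-day mean; 30 walkers ("N =30 participants each group"). There is no figure of the plan's own to reproduce: "Sample size calculations for effectiveness will be not performed", and no step mean, SD or week-to-week reliability is given.

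**Assumptions (not in the article).** Weekly mean steps are normal across the plant with mean μ and SD 2,500 or 3,000. Correlation between two weeks is r = 0.7 to 0.9. Screening-week values are confined to 0-7,500. The programme has zero effect and there is no time trend.

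**Formulas.** Let a = (0 − μ)/SD and b = (7,500 − μ)/SD.
- Expected rise = (1 − r) × SD × [φ(b) − φ(a)] / [Φ(b) − Φ(a)].
- SD of individual change = √[(1 − r)² × V + SD² × (1 − r²)], where V is the variance of the truncated screening week.
- P(mean change > 0) = Φ(rise / (SD of change / √30)).

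**Three worked cases.**
- μ = 4,500, SD 2,500, r = 0.9: a = −1.8, b = 1.2. Ratio = (0.1942 − 0.0790)/(0.8849 − 0.0359) = 0.1357. Rise = 0.1 × 2,500 × 0.1357 = 34. SD of change 1,105, SE 1,105/√30 = 202. P = Φ(0.17) = 57%.
- μ = 6,000, SD 3,000, r = 0.7: a = −2, b = 0.5. Ratio = (0.3521 − 0.0540)/(0.6915 − 0.0228) = 0.4458. Rise = 0.3 × 3,000 × 0.4458 = 401. SD of change 2,212, SE 404. P = Φ(0.99) = 84%.
- μ = 8,500, SD 3,000, r = 0.7: a = −2.833, b = −0.333. Ratio = (0.3774 − 0.0072)/(0.3694 − 0.0023) = 1.008. Rise = 0.3 × 3,000 × 1.008 = 907. SD of change 2,193, SE 400. P = Φ(2.27) = 99%.

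**Range over SD 2,500-3,000 and r 0.7-0.9.**

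| Assumed plant mean (steps/day) | Spurious rise (steps/day) | P(mean change of 30 > 0) |
|---|---|---|
| 4,500 | 34-131 | 57%-63% |
| 6,000 | 108-401 | 70%-84% |
| 7,500 | 198-695 | 83%-96% |
| 8,500 | 267-907 | 90%-99% |

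The lower bound matters only at low plant means. Without it the range at 6,000 becomes 72%-87%.

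**Other outcomes.** The SF-36, walk test, blood pressure and body measures are not selection variables. With no effect and no time trend, each moves in the favourable direction with probability about 50%.

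**Between-arm comparison.** Both randomised arms come from the same selected pool, so the expected artefact cancels. A zero-effect programme gives a difference above 0 with probability 50%, and a 95% CI wholly above 0 with probability about 2.5%.

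**The case against.** The strongest reply is that this is one loose clause in a comparative trial. The article randomises, frames its aims against control, collects control steps at 12 weeks, and plans means and confidence intervals for every outcome. That is right: the defect lies in this strand, not in the design.

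A reader might infer more than the article supports:

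- **That the plan would declare an inert programme feasible.** The article gives no pass/fail rule. Positive change is one of three strands and is never called sufficient; poor adherence or satisfaction could still count against the programme.
- **That some outcome is nearly certain to improve by chance.** This needs a rule that any one of many independent outcomes will do. No such rule is stated, the wording is singular, and SF-36 domains or body measures would hardly be independent.
- **That a false positive step change is nearly certain.** This holds only if the plant mean is at or above the cut-off. The Introduction describes this workforce as sedentary, and at 4,500 steps/day the probability is not far above 50%.
- **That the selection argument covers every outcome.** It applies to step count. Other measures would be affected only as far as their week-to-week error follows that of steps.

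Two further points stand. In the screening week participants reset, read and log their own counts, and reactivity could raise baseline and offset part of the artefact. Progression thresholds may sit in a full protocol, so their absence from an article is not a fault. One might also read the Screening wording as implying a separate baseline after exclusion. However, Preparation of participants treats the same seven days as baseline.

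**Conclusion.** The point holds in limited form. As written, the third strand is a within-arm change that makes no use of the control arm. For step count, selection on the baseline week tilts it towards a positive result under zero effect. The direction is the same in every case examined. The size rests on assumed values and runs from slight, if the plant averages far below 7,500 steps/day, to large, if it averages near or above that figure. Reactivity, which the article gives no means of quantifying, would reduce it. For the remaining outcomes the strand simply cannot separate effect from chance or time trend. The remedy is inexpensive because the control data are already planned.

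**What to change.** 1. Remove the positive-change clause from the feasibility criteria, or restate it as the walking-minus-control difference in the 12-week outcome, adjusted for baseline, with a 95% CI. If it is kept, name the outcome and the favourable direction, since improvement in blood pressure, BMI, body fat and waist is a fall.
2. Judge feasibility on adherence and satisfaction, as already planned, together with recruitment and retention.
3. State that the within-arm step change will not be interpreted, nor carried into the future trial's sample size, because the baseline week was also the selection week.
4. Reconcile Screening with Preparation of participants on whether exclusion comes before baseline measurement or uses it.

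**Cost.** Wording only; no extra participants, visits or data. The downside is precision. In the case μ = 6,000, SD 3,000, r = 0.7, the baseline-adjusted difference has SE = 3,000 × √(1 − 0.49) × √(2/30) = 553 steps/day, against 404 for the within-arm change. With 30 per arm, the between-arm estimate may therefore look less favourable than the within-arm change.

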## Procedure

### Preparation of participants

All potential participants will be instructed to wear the pedometer on the waistband of their clothing for seven days, based on previous study protocols [96-99] in order to establish baseline step-counts during normal daily activity. Tudor-Locke and Bassett [52] have classified pedometer-determined PA in adults by an average step count of less than 5,000 steps/day as a sedentary lifestyle, and 5,000 to 7,499 steps per day as low activity; therefore, participants who accumulate an average baseline step count of 7,500 steps per day or more will be excluded; remaining participants will be randomized to one of the two groups. Baseline outcomes measures were collected during the seven days pedometer assessment including the primary and secondary outcomes. After randomization, all participants will attend a 30 minute education session on the health benefits of being physically active, then participants in the walking group will receive a brief intervention group session of up to 70 minutes, including a 10 minute self-efficacy walk, a 30 minute session focussing on physical activity behaviour change, and 30 minutes focused on the education resource material (physical activity and PA booklet). This intervention session will be based on the Back2Activity protocols [100] and conducted by physiotherapists (including one with training in motivational interviewing), and student researcher.

